### Reference standard for presence/absence of heart failure

An independent expert consensus panel comprising three cardiology specialists will determine the final diagnosis of LVSD or not (ejection fraction <40%) and HF or not, based on internationally accepted definition [47], with differences resolved by consensus. In order to reach an accurate diagnosis the consensus panel need all clinical and test information but this could introduce incorporation bias. To minimise this but provide fuller information for the consensus panel they will receive information in 3 steps. In Step 1, echocardiography results will be provided along with all other clinical information except the NT-proBNP test results and clinical variables included in the CDR, namely, history of myocardial infarction, gender, basal lung crepitations and ankle oedema. The consensus panel will reach a decision on whether or not heart failure is present initially without these data. In Step 2, CDR clinical variables will then be made available to the expert panel and comparison made with the initial assessment. In Step 3, NT-proBNP test results will be provided and the consensus panel asked whether this changes their opinion. The primary reference standard for the study is therefore Step 3 where all clinical and test information is available to the consensus panel. However, we will also be able to accurately estimate any incorporation bias that may have related to this reference standard based upon Steps 1 and 2.

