### Patient eligibility

Patient eligibility will be determined by the GP using information from clinical history and examination and recording clinical judgment via a GP web-based database. The eligibility criteria will be confirmed by investigation and specialist interpretation of clinical assessments. Objective evidence of HF (reference standard) will be determined by a specialist panel that will validate previous diagnosis and investigations.

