### Primary and secondary endpoints

Primary outcomes include:

• Test performance of the CDR, estimating the sensitivity and specificity, positive predictive value and negative predictive value of the CDR for diagnosis of HF in symptomatic patients presenting with shortness of breath, lethargy, or ankle oedema of over 48 hours duration

• Test performance of the diagnostic accuracy of NT-proBNP for diagnosis of HF in symptomatic patients, including sensitivity, specificity, positive predictive value and negative predictive value

• Proportion of patients with LVSD or not (ejection fraction <40%) and HF or not

Secondary outcomes include:

• Combination of the CDR and NT-proBNP

• Modelling of CDR test performance and epidemiological data to ascertain the most cost effective strategy in the diagnosis of HF in primary care, incorporating data on quality of life (EQ-5D and SF12 questionnaires), clinical events and health care resource use

• Reliability of GP clinical judgment alone in diagnosing HF

• Reliability of individual clinical features

• Reliability of ECG interpretation

• Estimation of the best performing cut-offs for NT-proBNP to maximise diagnostic yield and for maximizing cost-effective referrals

• Determine the use of variable echocardiographic markers of diastolic function in the diagnosis of HF with preserved ejection fraction

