### Clinical judgment

During the initial consultation, GPs will have identified a patient as eligible for referral to one of the two research assessment clinics (i.e. recent new onset shortness of breath, lethargy or ankle oedema of over 48 hours duration). They will then complete the two clinical judgment sections of the online web-based Case Report Form: 1) details of symptoms, history and patient information, including the predictive clinical features of the CDR; 2) whether they would have made a clinical diagnosis of HF or not and what they would have done routinely with this patient (i.e. investigate, initiate referral, treat, follow-up). Following diagnostic assessment at the research assessment clinic, the NP results will be fed back to GPs and based on those results, GPs will be asked what they would do (refer or not refer to Echo) and if they would amend their original diagnosis.

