### Limitations

This study has potential limitations that apply to validating CDRs. Reference standard misclassification is an inherent problem of diagnostic accuracy studies that may introduce bias [57,58]. The prospective study design will allow us to ensure that all symptomatic patients presenting with new onset symptoms suggestive of heart failure will receive identical standardised assessments.

This will ensure that all patients are diagnosed in a consistent manner in order to avoid introducing variation into the reference standard. Our reference standard also incorporates multiple assessments, thereby minimising potential reference standard misclassification [59]. Another possible limitation concerns incorporation bias. This occurs when knowledge of the result of the index test influences the reference standard test. The CDR incorporates variables from the history, examination and tests that would normally be included in a reference standard. To minimise the potential for bias our expert consensus panel will initially receive the clinical information and investigation results about the patient with the exception of the information that comprises the CDR (namely history of myocardial infarction; gender; basal lung crepitations and ankle oedema) and the NT-proBNP result. They will be asked to reach a decision on whether or not HF is present initially without these data. They will then be given the clinical features of the CDR score and asked if this influences their decision, and then the results of the NT-proBNP test. This stepped reference standard will allow us to quantify the effects of any incorporation bias.

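### The list of items withheld from the diagnostic panel omits the GP's own judgment, although that judgment is assessed against the panel's diagnosis

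*Protocol article*

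**What the plan says.** **What the panel receives.** Under Reference standard for presence/absence of heart failure, Step 1 is defined by its exceptions: "echocardiography results will be provided along with all other clinical information except the NT-proBNP test results and clinical variables included in the CDR". The CDR variables are released at Step 2 and NT-proBNP at Step 3. The same section then states: "The primary reference standard for the study is therefore Step 3 where all clinical and test information is available to the consensus panel". The Limitations section describes the Step 1 packet again: "our expert consensus panel will initially receive the clinical information and investigation results about the patient with the exception of the information that comprises the". That sentence goes on to name the same two exceptions, the decision rule's items and the peptide result.

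**What the GP records.** Under Clinical judgment, the GP completes two parts of the web-based form. The first holds symptoms, history and the CDR features. The second holds "whether they would have made a clinical diagnosis of HF or not and what they would have done routinely with this patient". After the peptide result is fed back, the GP is asked whether they would refer for echocardiography and "if they would amend their original diagnosis".

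**How GP judgment is used.** It appears in three places:
- Primary and secondary endpoints lists "Reliability of GP clinical judgment alone in diagnosing HF".
- The Background says that the CDR's impact potential will be shown by whether its sensitivity and specificity exceed those of unaided GP decisions.
- Health economic analysis uses GP-reported judgment to represent current practice.

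**The concern.** The Limitations section explains incorporation bias as knowledge of an index test result influencing the reference standard. The plan protects two index tests against it, the CDR and NT-proBNP. GP judgment is a third: its sensitivity and specificity need a reference diagnosis, and the panel's is the only one in the protocol. Neither statement of the exceptions covers it.

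If the panel saw the GP's opinion and sometimes deferred to it, apparent GP accuracy would rise. The comparison with the CDR would then move in the GP's favour, as would the current-practice arm of the model.

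A further, conditional point concerns the GP's post-peptide answer. If it reached the panel before Step 3, it could signal the NT-proBNP result and weaken the Step 1 and Step 2 comparisons that are meant to quantify incorporation bias.

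**Working it through.** **1. The text.** Both descriptions of Step 1 start from everything clinical and remove named items. Read literally, anything clinical that is not named goes forward. The GP's two sets of answers are not named. Elsewhere the protocol states blinding where it is wanted: for the ECG readers (ECG assessment and interpretation) and for the cardiologist who validates the sound recordings (Diagnostic assessment).

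**2. Why the steps cannot detect it.** Moving from one step to the next shows the effect of the information released in between. The GP's initial opinion, if present, would be there at Steps 1, 2 and 3, so no contrast between steps isolates it.

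**3. Planning figures.** Sample size gives 500 patients, prevalence 30%, and CDR sensitivity 94% and specificity 48%. That means 150 patients with HF and 350 without, of whom 141 and 182 respectively are CDR-positive. The stated precision reproduces:
- sensitivity: 1.96 × √(0.94 × 0.06/150) = 3.8 points (stated: within 4)
- specificity: 1.96 × √(0.48 × 0.52/350) = 5.2 points (stated: within 6)

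The point does not depend on these precision figures. The protocol gives no GP accuracy, so the rest is illustration.

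**4. Effect on the GP.** Let *a* be the HF patients the GP misses, *b* the GP's false positives, and *f* the share of GP–panel disagreements that move to the GP's call (assumed).
- Apparent sensitivity = (150 − *a* + *fb*) / (150 − *fa* + *fb*)
- Apparent specificity = (350 − *b* + *fa*) / (350 + *fa* − *fb*)

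For any *f* above zero both rise, because misses and false positives are turned into agreements.

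Assume GP sensitivity 60% and specificity 80%, so *a* = 60 and *b* = 70. At *f* = 10%, 6 patients leave the reference-positive group and 7 enter it:
- sensitivity = (90 + 7)/151 = 64.2%
- specificity = (280 + 6)/349 = 81.9%

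Other assumed GP accuracies at *f* = 10%:

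| Assumed GP sens/spec | Apparent sens/spec |
|---|---|
| 60/70 | 65.0/72.6 |
| 70/60 | 74.6/63.0 |
| 80/50 | 83.6/53.1 |

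**5. Effect on the CDR.** This depends on how CDR and GP results are related given true status. Take GP 60/80 and *f* = 10%.
- *Independent:* CDR sensitivity = (141 − 6 × 0.94 + 7 × 0.52)/151 = 139.0/151 = 92.1%. The CDR's sensitivity lead falls from 34.0 to 27.8 points (30.9 at *f* = 5%, 21.7 at *f* = 20%). With a GP at 75/70 it falls from 19.0 to 12.7 at *f* = 10%.
- *Positively related:* suppose the CDR is positive in 85% of HF patients the GP misses and 100% of those the GP detects, and in 90% of GP false positives and 42.5% of GP true negatives. The margins are unchanged: 51 + 90 = 141 and 63 + 119 = 182. CDR sensitivity = (141 − 5.1 + 6.3)/151 = 94.2% and specificity = (168 − 0.7 + 0.9)/349 = 48.2%. Neither falls. The lead still narrows, to about 29.9 points, through the GP's gain alone.

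**The case against.** **The opinion may never have been meant for the panel.** No section places either GP answer in the packet. The second part of the GP form is a hypothetical research response, and the Limitations section speaks of clinical information and results about the patient, which can be read as leaving it out. The panel is also called independent. This stands to the extent that nobody can say from the protocol that the panel is unblinded or that the standard contains the GP's diagnosis. It does not remove the point. A rule that passes on everything except named items, given twice, fixes what is withheld, and the history the panel needs sits on the same form as the opinion.

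**Patient eligibility does not settle it.** A reader might infer sight of the GP's diagnosis from the statement that HF status "will be determined by a specialist panel that will validate previous diagnosis and investigations". That more naturally refers to patients with an existing HF label but no objective evidence, whom Exclusion criteria keeps in the study. The point does not rest on it.

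**The peptide leak is conditional.** It needs the amended opinion to be in the packet, and to be there before Step 3. The protocol states neither. Step 3 discloses NT-proBNP by design, so a leak would not alter the content of the primary standard.

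**The panel has little reason to defer.** Three cardiologists with echocardiography, using a definition that requires objective cardiac abnormality, may rarely follow a GP's pre-test view. This is fair, and *f* may be small. It is unknown, and the design gives no way to estimate it.

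**GP judgment is secondary.** The kappa analysis in Statistical analysis compares GP with researcher and does not use the panel. That is correct and limits the importance of the point. The sensitivity and specificity comparison promised in the Background still needs the panel.

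**Conclusion.** The point holds as a gap in the withholding rule. Followed literally, the rule permits incorporation bias in the GP comparator, and the three-step design would not detect it. The direction for the GP is clear if deference occurs: apparent sensitivity and specificity both rise. The size cannot be derived from the protocol. A gain of about 4 points in sensitivity and 2 in specificity rests on an assumed GP accuracy of 60/80 and an assumed 10% of disagreements moved.

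A reader might go further and conclude that the bias also lowers the CDR's own accuracy. That follows only if GP and CDR results are independent given true status, which is doubtful because the same GP records the CDR features. In the related case above CDR sensitivity does not fall. Nor does the protocol support saying that Steps 1 and 2 are contaminated by NT-proBNP; that is only a possibility.

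The main effect is on the secondary GP-accuracy outcome, the CDR-versus-GP comparison and the economic model. Primary CDR and NT-proBNP accuracy is affected only indirectly. This is a worthwhile correction but not a threat to the primary analysis.

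**What to change.** Add one sentence to Reference standard for presence/absence of heart failure, and match it in Limitations: at all three steps the panel packet excludes the GP's diagnosis, intended action, post-peptide decision and amended diagnosis. Only history, examination and investigation data go forward, with the CDR items released at Step 2 and NT-proBNP at Step 3 as planned.

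The cost is that sentence and a change to how the packet is extracted from the database. It needs no extra patients, visits or staff, and the sample size is unchanged. It has to be in place before the panel reviews cases, because an opinion once seen cannot be removed by analysis.

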### Statistical analysis

Data will be analysed using SAS and STATA software. Patients with symptoms of HF that are referred to Echo via the CDR will be classed as Test disease present and the remaining patients classed as Test disease absent. The Observed disease present or absent will be determined by the expert panel following Echo and other clinical assessments. Crosstabulation of Test versus Observed disease status will enable calculation of sensitivity (true positive rate), specificity (true negative rate), positive predictive value (PPV: proportion with a positive test result who actually have the target condition), negative predictive value (NPV: proportion with a negative test result who do not have the target condition), and likelihood ratios for testing the performance of the CDR. 95% confidence intervals for these performance statistics will be calculated using the binomial exact method.

To confirm whether the NT-proBNP cut-offs in the CDR are optimal in the real life clinical setting, an additional ROC curve analysis of NT-proBNP to predict HF will be performed. Analysis will compare the CDR performance against the step 1 reference test alone; against the step 1 reference test plus clinical features of the CDR (step 2); and against the step 1 reference test plus the CDR and the NT-proBNP result (the reference standard, step 3). Step 3 is the primary reference standard for analysis. This will allow us to: 1) quantify the effects of any incorporation bias; 2) explore the impact that availability of NT-proBNP test result would have on the reference standard diagnosis of HF. Comparison of the GPs’ and researcher’s clinical findings (lung crepitations, ankle oedema, decision to refer to Echo) will be assessed by the kappa statistic. Logistic regression will be used to identify which diastolic parameters of echocardiography are independently associated with the diagnosis of heart failure with preserved ejection fraction.

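### The primary reference diagnosis (Step 3) is made with the NT-proBNP result known, and the check against earlier, blinder decisions is stated for the CDR only, not for NT-proBNP accuracy, its cut-offs or the CDR versus NT-proBNP comparison

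*Protocol article*

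**What the plan says.** The section Reference standard for presence/absence of heart failure has the panel decide three times.

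- **Step 1:** echocardiography and the rest of the patient's work-up, "except the NT-proBNP test results and clinical variables included in the CDR, namely, history of myocardial infarction, gender, basal lung crepitations and ankle oedema".
- **Step 2:** "In Step 2, CDR clinical variables will then be made available to the expert panel and comparison made with the initial assessment".
- **Step 3:** "In Step 3, NT-proBNP test results will be provided and the consensus panel asked whether this changes their opinion".

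The same section makes the last decision primary: "The primary reference standard for the study is therefore Step 3 where all clinical and test information is available to the consensus panel". The Statistical analysis section repeats this: "Step 3 is the primary reference standard for analysis". The reference standard section acknowledges incorporation bias and says of the stepped design that "we will also be able to accurately estimate any incorporation bias".

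The Statistical analysis section then says "Analysis will compare the CDR performance against the step 1 reference test alone", and likewise against Steps 2 and 3. That sentence is about the CDR. The ROC analysis of NT-proBNP, in the same paragraph, names no step. Primary and secondary endpoints lists as a primary outcome "Test performance of the diagnostic accuracy of NT-proBNP for diagnosis of HF in symptomatic patients". The objectives at the end of the Background include comparing the CDR with a natriuretic peptide assay alone (objective 1) and finding the most reliable peptide cut-offs (objective 3).

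**The concern.** Incorporation bias arises when the result under evaluation helps to decide the reference diagnosis. At Step 3 the panel is handed the NT-proBNP result and asked whether it alters the diagnosis. NT-proBNP is then judged against that diagnosis. A panel that responds to the result will tend to move toward agreeing with it, so the sensitivity and specificity of NT-proBNP would tend to be too high. A cut-off chosen by ROC against Step 3 may partly reproduce the level that the panel itself regards as abnormal.

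The stepped design could expose this, but the stated use of Steps 1 and 2 as references covers the CDR and not NT-proBNP alone, which is the test most directly affected. The consequence may travel further. The Health economic analysis section plans to estimate an optimal peptide threshold for referral, so inflated NT-proBNP accuracy could reach that result too.

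**Working it through.** **What the panel knows, and which analysis uses which reference**

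| Step | CDR clinical items known | NT-proBNP known |
|---|---|---|
| 1 | no | no |
| 2 | yes | no |
| 3 (primary) | yes | yes |

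| Analysis | Reference stated |
|---|---|
| CDR accuracy | Steps 1, 2 and 3, with Step 3 primary |
| NT-proBNP accuracy (primary outcome) | none named, so Step 3 by the general rule |
| NT-proBNP ROC and cut-offs (objective 3) | none named, so Step 3 |
| CDR versus NT-proBNP (objective 1) | none named, so Step 3 |

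**The plan's own precision figure.** Sample size gives 500 patients, 30% prevalence, and CDR sensitivity 94% and specificity 48%. That is 0.30 × 500 = 150 with heart failure (HF) and 350 without. The half-width is 1.96 × √(p(1−p)/n).

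- Sensitivity: 1.96 × √(0.94 × 0.06 / 150) = 3.8 points, consistent with the stated 4%.
- Specificity: 1.96 × √(0.48 × 0.52 / 350) = 5.2 points, consistent with the stated 6%.

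These figures reproduce and this point does not affect them. They are targets for the CDR, so they give only a rough scale for NT-proBNP.

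**Illustration for NT-proBNP.** The article gives no rate at which the panel changes its decision. Assume that NT-proBNP has sensitivity 85% and specificity 60% against Step 2, and that a fraction f of discordant patients switch at Step 3 toward the test. The expected counts at Step 2 are TP 127.5, FN 22.5, FP 140, TN 210. After switching:

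- sensitivity = (TP + f·FP) / (TP + f·FP + (1−f)·FN)
- specificity = (TN + f·FN) / (TN + f·FN + (1−f)·FP)

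| f | Sensitivity | Specificity |
|---|---|---|
| 0 | 85.0% | 60.0% |
| 0.10 | 141.5 / 161.75 = 87.5% | 212.25 / 338.25 = 62.7% |
| 0.20 | 155.5 / 173.5 = 89.6% | 214.5 / 326.5 = 65.7% |

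Other starting values at f = 0.20:

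- From an assumed 80%/70%: 141/165 = 85.5% and 251/335 = 74.9%.
- From the 98% sensitivity cited in the Background, with an assumed specificity of 60%: 175/177.4 = 98.6% and 210.6/322.6 = 65.3%. Sensitivity then hardly moves, while specificity gains about 5 points.

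**Direction for the CDR.** Start from 94%/48%, that is TP 141, FN 9, FP 182, TN 168.

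- If 20% of discordant patients switch toward the CDR result: 177.4/184.6 = 96.1% and 169.8/315.4 = 53.8%, which is higher.
- If 10 patients who are CDR-positive on a clinical item and HF at Step 2 are changed to no HF by a low NT-proBNP: 131/140 = 93.6% and 168/360 = 46.7%, which is lower. With 20 such patients: 121/130 = 93.1% and 168/370 = 45.4%.

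The bias for the CDR can therefore go either way.

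**The case against.** The protocol does not hide the problem. It names incorporation bias, justifies Step 3 by the panel's need for full information, builds the stepped panel to expose the bias, and discusses it again under Limitations. The CDR, the study's main test, is to be checked against all three steps. The Statistical analysis section also plans to explore how having the NT-proBNP result affects the reference diagnosis. All of this stands, and the CDR's accuracy does have a declared check.

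Which recorded decision serves in supporting analyses is often left to an analysis plan, and none is shown here. That is fair for supporting analyses. It does not reach the choice of Step 3 as primary, which this article fixes for every analysis.

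A change of diagnosis at Step 3 may also be a true correction. The Discussion suggests that a raised peptide may itself be diagnostic in HF with preserved ejection fraction. If so, Step 2 misclassifies some of those patients and would understate NT-proBNP accuracy. This stands as a cost of using Step 2. It is also a question that comparing Step 2 with Step 3 can address. Against it, the criteria under Definition of heart failure (symptoms, signs, objective cardiac abnormality) do not call for a peptide result, and Step 2 withholds nothing else.

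Two stronger readings are tempting. One is that the bias inflates all the accuracy results, the CDR's included. The working shows that CDR accuracy can fall. The other is that NT-proBNP must gain over the CDR because it is shown last. The CDR also contains NT-proBNP and its clinical items are known from Step 2, so both tests are incorporated and the net effect cannot be determined from the documents.

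**Conclusion.** The point holds in a limited form. A primary outcome and a stated objective concern NT-proBNP, and by default they are judged against a diagnosis made with the NT-proBNP result known, with no stated analysis against a diagnosis made without it. For NT-proBNP alone the expected bias is upward. For the CDR, and for the CDR versus NT-proBNP comparison, the direction is undetermined.

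The documents do not fix the size. The gains of 2.5 to 4.6 points in sensitivity and 2.7 to 5.7 in specificity rest on an assumed 85%/60% starting point and on 10% to 20% one-way switching. They shrink if the panel rarely changes its decision and vanish if it never does. Where sensitivity is already very high, its gain is small.

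The claim that the bias can be accurately estimated is too strong. The same panel revises its own earlier decision and may anchor on it. Each step also adds real diagnostic information: Step 1, for example, lacks crepitations and oedema, which are signs of the kind the HF definition asks for. A difference between steps therefore mixes bias with information. This is a worthwhile, low-cost improvement and does not invalidate the study.

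**What to change.** All three panel decisions are already to be recorded, so no new data are needed.

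1. Use Step 2 (everything except NT-proBNP) as the reference for NT-proBNP accuracy and for the ROC and cut-off analyses, and report Step 3 alongside.
2. Report the CDR versus NT-proBNP comparison against Steps 1, 2 and 3, and keep Step 3 as the final clinical diagnosis. Making Step 1 the sole reference for this comparison is not advised, because it would trade incorporation bias for misclassification from withheld signs and history.
3. Report the number and direction of diagnosis changes at each step. Replace the claim that "we will also be able to accurately estimate any incorporation bias" with a statement that the steps show how sensitive the results are to it.

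The cost is revised wording and a few extra tables. Reported NT-proBNP accuracy may be somewhat lower, and Step 2 may misclassify some HF with preserved ejection fraction, which is why Step 3 should be shown beside it.

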### Inclusion criteria

• All patients 55 years of age or over presenting to their GP with new onset symptoms of breathlessness, lethargy, or ankle oedema of over 48 hours duration, with no obvious recurrent, acute or self-limiting cause

• Able to give informed consent

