### Definition of heart failure

Clinical HF will be defined using the European Society of Cardiology guidelines: “HF is a syndrome in which the patients should have the following features: symptoms and signs of HF and objective evidence of an abnormality of the structure or function of the heart at rest” [14].

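### The stepped panel comparison cannot accurately estimate incorporation bias, because Step 1 withholds signs that the study's own heart failure definition includes

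*Protocol article*

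**What the plan says.** All references are to the protocol article.

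- *Definition of heart failure* requires "symptoms and signs of HF and objective evidence of an abnormality of the structure or function of the heart at rest".
- *Reference standard for presence/absence of heart failure* has three specialists decide in three steps. At Step 1 they receive the echocardiogram and the remaining findings "except the NT-proBNP test results and clinical variables included in the CDR, namely, history of myocardial infarction, gender, basal lung crepitations and ankle oedema". Step 2 then releases the CDR variables, and Step 3 adds NT-proBNP. Step 3 is the primary reference standard.
- The same section gives the reason for the steps: "In order to reach an accurate diagnosis the consensus panel need all clinical and test information but this could introduce incorporation bias". It then states the benefit, drawn from Steps 1 and 2: "we will also be able to accurately estimate any incorporation bias".
- *Statistical analysis* plans to compare CDR accuracy against each of the three steps. That section and *Limitations* both say that the effects of incorporation bias will thereby be quantified.
- *Limitations* describes incorporation bias as arising when knowing the index test result influences the reference standard. It acknowledges that the CDR uses items which a reference standard would normally contain.

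**The concern.** To read the difference between steps as a measure of bias, Step 1 must be a valid benchmark that lacks only the contamination. It is not one. The panel must decide whether HF is present while two signs that can form part of the definition are hidden. When such a sign appears at Step 2 and the diagnosis changes, the panel may be applying the definition properly, may be influenced by an index-test item, or both.

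The mixing is related to the CDR result. Under *Clinical decision rule*, basal crepitations alone, or ankle oedema in a man, are enough for a positive rule, so new HF diagnoses prompted by these signs tend to fall in CDR-positive patients.

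The stepped comparison is the article's stated means of measuring incorporation bias, and the primary standard contains every CDR component. If the whole shift is reported as bias, it may be overstated. If Step 1 accuracy is reported as the bias-free figure, a less accurate standard is given an authority it lacks.

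**Working it through.** **1. The plan's own figures.** *Sample size* gives N = 500, prevalence 30%, sensitivity 94% and specificity 48%. This means 150 patients with HF and 350 without:

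- true positives 0.94 × 150 = 141, false negatives 9
- true negatives 0.48 × 350 = 168, false positives 182

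Normal-approximation half-widths are 1.96 × √(0.94 × 0.06/150) = 3.8 points and 1.96 × √(0.48 × 0.52/350) = 5.2 points. Both lie within the stated 4% and 6%. The point does not depend on this calculation; the table serves only as a base for illustration.

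**2. What a given shift can mean.** The documents give no reclassification counts, so those below are assumptions. Take the planned table as the Step 2 result. Suppose that between Steps 1 and 2, 15 CDR-positive patients move from non-HF to HF and 10 CDR-negative patients move from HF to non-HF. Against Step 1:

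- sensitivity = (141 − 15)/[(141 − 15) + (9 + 10)] = 126/145 = 86.9%
- specificity = (168 − 10)/[(168 − 10) + (182 + 15)] = 158/355 = 44.5%

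The observed shifts are 94.0 − 86.9 = 7.1 points and 48.0 − 44.5 = 3.5 points.

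Now let a share f of the moves be correct classification and the rest wrong, with patients who do not move correctly classified. Put u = 15(1 − f) and w = 10(1 − f). Then true sensitivity = (141 − u)/(150 − u + w) and true specificity = (168 − w)/(350 + u − w). Bias is the Step 2 value minus the true value.

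| Share of moves correct (f) | Bias in sensitivity (points) | Bias in specificity (points) |
|---|---|---|
| 0% | 7.1 | 3.5 |
| 25% | 5.3 | 2.6 |
| 50% | 3.5 | 1.8 |
| 75% | 1.7 | 0.9 |
| 100% | 0.0 | 0.0 |

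The observed tables at Steps 1 and 2 are identical in every row. Nothing the article says is recorded identifies f.

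**3. How the shift varies with the assumed counts.** With 0 to 30 CDR-positive patients moving to HF and 0 to 15 CDR-negative patients moving out, the shift runs from 0 to 11.8 points in sensitivity and from 0 to 6.1 points in specificity.

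**4. A shift made only of correct completion.** Suppose 15 or 30 patients (10% or 20% of the 150), all CDR-positive, become HF only once the hidden signs are shown, and all these changes are correct. Step 1 then gives:

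- sensitivity 126/135 = 93.3% or 111/120 = 92.5%, against 94.0%
- specificity 168/365 = 46.0% or 168/380 = 44.2%, against 48.0%
- positive predictive value 126/323 = 39.0% or 111/323 = 34.4%, against 141/323 = 43.7%

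Most of the fall in predictive value is lower prevalence. At 27% or 24% prevalence (135/500 or 120/500), with sensitivity and specificity held at 94% and 48%, it is already 0.2538/(0.2538 + 0.3796) = 40.1% or 0.2256/(0.2256 + 0.3952) = 36.3%.

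**The case against.** **Incorporation as the article defines it.** A panel that changes its mind after seeing a CDR item is what the article means by incorporation, and Steps 1 and 2 are built to catch it. This stands. A change can be sound diagnosis and incorporation at once, so a reader who infers that Step 1-to-2 changes are merely the definition being completed, and hence not bias, goes further than the documents allow. Equally, the objection does not show that the whole shift is distortion.

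**Other information stays visible.** A reader might also infer that a patient with an abnormal echocardiogram cannot be called HF at Step 1 and must become HF at Step 2. The documents do not support that. The article says "In Step 1, echocardiography results will be provided along with all other clinical information"; *Diagnostic assessment* lists a chest x-ray, ECG and clinical examination; and *Background* names further signs. The panel works by consensus, not by algorithm. Only patients whose qualifying signs are mainly the withheld ones are affected.

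**Reach.** NT-proBNP is not a sign in the definition, so the argument from signs does not touch the Step 2-to-3 contrast. Step 2 also releases sex and history of myocardial infarction, which are not signs.

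**Size.** The counts are assumed. In calculation 4, sensitivity moves 0.7 to 1.5 points and specificity 2.0 to 3.8, less than the stated precision. Nor need every affected patient be CDR-positive: under the rule, a woman with ankle oedema also needs a raised peptide, a previous infarction or crepitations. So no claim of a large spurious bias can be made.

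**Unmasking.** Entry requires "new onset symptoms of breathlessness, lethargy, or ankle oedema of over 48 hours duration", so a patient shown with neither of the first two must have oedema. This concerns only patients whose sole entry symptom is oedema. Neither their number nor the way symptoms are presented to the panel is given, so it remains a possibility and not a finding.

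**Conclusion.** The claim of accurate estimation, and the matching claims of quantification in *Statistical analysis* and *Limitations*, describe a property the design lacks. The article's own statement that accuracy needs all information makes Step 1 a less accurate standard, not an unbiased benchmark. The conclusion rests on two textual facts: the definition includes signs, and two signs are withheld. It does not rest on the assumed counts, which only show that any observed shift is compatible with a bias from none to all of it, provided that movers are correctly classified at one of the two steps and non-movers at both. The number of patients concerned, and so the practical size, cannot be determined from the documents.

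A reader might conclude that the stepped design is worthless or that the primary analysis fails. Neither follows. The comparison remains a useful sensitivity analysis, and Step 3 remains the declared primary standard with its trade-off disclosed. What changes is the conclusion that may be drawn from the comparison.

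**What to change.** 1. Replace the claim in all three sections. State that the Step 1–3 comparison shows how sensitive CDR accuracy is to the information given to the panel, that the Step 1-to-3 shift is not a point estimate of incorporation bias, and that Step 1 accuracy is not the bias-free figure.
2. At Step 1, before the CDR variables are released, have the panel also record (a) whether an objective cardiac abnormality is present and (b) whether the HF decision depends on the withheld signs.
3. Report Step 1-to-2 and Step 2-to-3 reclassification separately, by CDR result and by these two items.
4. Treat changes in patients with an abnormality already recorded as ambiguous. Count them once as correct classification and once as incorporation, and report the resulting range for the bias. They should not be excluded from the bias: the echocardiogram is the same at both steps, so counting only changes in the cardiac finding would push the estimate towards zero. It would also leave out the patient with an abnormal echocardiogram who is tipped to HF by a CDR sign.

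The presenting complaint should not be held back until Step 2 to prevent unmasking. The definition also requires symptoms, so this would make Step 1 less complete still.

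The cost is two extra items on the panel form, one extra cross-tabulation and a less favourable claim. No additional visits, patients or panel members are needed.
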